#### Statistical analysis

Data analysis will be on an intention-to-treat basis and consist of univariate analysis between randomised groups on the primary and secondary outcomes. A more in-depth analysis will use longitudinal methods to account for correlations within families and to examine changes over time.

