## Methods/design

### Design

This study is a randomised controlled trial using three-groups: (1) Regional and remote intervention group, (2) Regional and remote control group, and (3) Metropolitan control group. Families will be classified as either metropolitan or regional and remote based on the ARIA+ score using the post code of the family's primary place of residence. Regional and remote families will be randomly allocated either to the intervention (1), or to a usual support control group (2). Metropolitan patients will receive support via traditional means as an additional usual support control group (3). This group will be used to provide a comparator against which the support provided to the regional and remote families can be judged.

The protocol for this study is registered with the Australian Clinical Trials Registry (ACTRN 012606000487516) and has been approved by the Royal Children's Hospital and Health Service District Ethics Committee and the University of Queensland Behavioural and Social Sciences Ethical Review Committee.

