### Data analysis

#### Sample size calculations

A total of 162 participants will be included in the study (based on data provided by the tertiary paediatric oncology referral centre this is feasible for a 24-month trial with a 20% refusal/attrition rate), 108 in the control group – 54 metropolitan and 54 regional and remote, and 54 in the regional and remote intervention group. Sample size calculations are given for the two main comparisons and economic analyses:

1. Regional and remote intervention group vs regional and remote usual support control group

- To test whether the provision of videotelephones to families in regional and remote areas can improve the health related quality of life of parents caring for a child with cancer over usual care, a unpaired t-test of the mean difference will be used [38]. This will be based on the SF-12 at week 12.

- As no paediatric caregiver research using the SF-12v2 has been undertaken in Australia to date, published evidenced available on paediatric parental caregiver burden in the US [39] and US norms [31] (Table 2) have been used as a guide for the sample size calculation. A clinically important difference would be to improve mean mental health related quality of life of parents (SF-12 Mental Component Summary [MCS]) in the intervention group by 7.5 points. This figure is further supported by calculation of SF-12v2 standard error of measurement [SEM], calculated as the standard deviation of an instrument multiplied by the square root of one minus its reliability coefficient [40]. With an SD of 10 and reliability coefficient of 0.86 [31], the MCS-12 has an SEM of 3.74. Evidence by Wywrich [41] supports the use of one SEM as an approximation of the *minimal *clinically important difference [MCID] of a psychometric instrument. Using this approximation, an improvement in MCS-12 of 7.5 represents two times the MCID, which is a large clinically important difference.

**Table 2 T2:** Published evidence available on the SF-12 health-related quality of life instrument.

Context	n	Details	Mean	SD
The impact of paediatric tracheotomy on parental caregiver burden and health status (US)[39]	154	PCS-12 MCS-12	50.5 35.8	11.3 11.4
US Norms[31]	7069	General US population		
		PCS-12	49.63	9.91
		MCS-12	49.37	9.75
		Depression		
		PCS-12	45.55	11.71
		MCS-12	37.40	10.76

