- Based on an improvement in MCS-12 mean in the intervention group of 7.5, and using SF-12v2 norm-based scoring methods (US general population SF-12v2 mean of 50 and SD of 10 [31]), at a power of 90% and a two-sided significance level of 1%, a sample size of 108 will be required, i.e. 54 in the intervention group and 54 in the control group.

2. Regional and remote intervention group vs metropolitan usual support control group

- To test whether the provision of videotelephones to families in regional and remote areas can improve the mental health related quality of life of parents to a level equivalent to that of metropolitan families receiving usual support, a test of equivalence will be used (according to the equivalence method described by Matthews [42]).

- With a two-sided significance level of 1%, sample size of 54, a mean difference between groups of zero and an equivalence bound of plus/minus 7.5, the study has a power of 87.2% for finding a genuine equivalence.

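### One of the two main comparisons, intervention versus metropolitan families, is not randomised, and the stated methods let baseline differences pass into its equivalence result

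*Protocol article*

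**What the plan says.** The Design section sets out three groups. Regional and remote families are allocated at random to intervention or usual support. The third group is formed by place of residence, using the ARIA+ score of the family's postcode: "Metropolitan patients will receive support via traditional means as an additional usual support control group". Its purpose is stated: "This group will be used to provide a comparator against which the support provided to the regional and remote families can be judged".

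The Sample size calculations section gives this group a leading role. It announces that "Sample size calculations are given for the two main comparisons and economic analyses", and the second of these is "Regional and remote intervention group vs metropolitan usual support control group". For parents in that metropolitan group, "receiving usual support, a test of equivalence will be used". The inputs are a two-sided significance level of 1%, a sample size of 54, a true difference of zero, bounds of ±7.5 and a stated power of 87.2%. No covariate is named. This comparison carries hypothesis 2, that videotelephone support to regional families is as effective as traditional support to metropolitan families.

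The Statistical analysis section says the analysis will be by intention to treat and will consist of "univariate analysis between randomised groups on the primary and secondary outcomes". A further longitudinal analysis is announced for two purposes, within-family correlation and change over time. The Measurement section lists demographics and baseline SF-12 among the data collected, and chart audits among the sources.

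**The concern.** Randomisation protects the comparison of the two regional groups. It does nothing for intervention versus metropolitan, where the groups are separated by where families live. Intention-to-treat does not help either, because it preserves a balance that was never created here.

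The one sentence on primary-outcome analysis speaks of randomised groups. Either it applies that label to a comparison that is not randomised, or it leaves that comparison with nothing but the equivalence test in the sample size section. On both readings, the article does not say how pre-existing differences between regional and metropolitan parents will be handled.

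Such differences are plausible on the article's own account: the Background describes distance, time, cost, transport and limited access to professionals as burdens on regional families. In an equivalence test they can act in two ways. They can push the groups apart and hide equivalence of support, or offset a real deficit and make the groups look equivalent. Hypothesis 2 would then be answered partly by who lives where.

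**Working it through.** **Inputs from the article (Sample size calculations).** 54 per group; SD 10; bounds ±7.5; true difference 0; stated power 87.2%; SEM of MCS-12 3.74, which the article uses as an approximate minimal clinically important difference.

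**Assumption.** The article gives no regional–metropolitan difference in MCS-12. Offsets of 1, 2 and 3.74 points (0.1, 0.2 and 0.374 SD) are illustrative.

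**Step 1: reproduce the stated power.** Two one-sided t-tests with 106 degrees of freedom.

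- Standard error = 10 × √(2/54) = 1.925.
- Critical value at 1% per one-sided test = 2.362.
- Equivalence is declared when the observed difference lies within about 7.5 − 2.362 × 1.925 = 2.95 points of zero, taking the sample SD as 10.
- With this limit held fixed, power at zero difference is 2Φ(2.95/1.925) − 1, about 87%. Integrating over the sampling distribution of the SD gives 87.2%, as stated.

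The match holds at 1% in each one-sided test (a 98% interval). At 0.5% per side the power would be 79.2%. The calculations below use the level that reproduces the article's figure.

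**Step 2: add an offset.** Let δ be the expected observed difference, that is, the true like-for-like difference plus the confounding offset. With the limit held fixed,

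P(declare equivalence) ≈ Φ((2.95 − δ)/1.925) − Φ((−2.95 − δ)/1.925).

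For δ = 2 this is Φ(0.49) − Φ(−2.57), about 0.68. The exact results are:

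| Offset (points) | Support truly equal: P(declare equivalence) | True deficit 7.5, favourable offset: remaining δ | P(false equivalence) |
|---|---|---|---|
| 0 | 87.2% | 7.5 | 1.0% |
| 1 | 82.2% | 6.5 | 3.5% |
| 2 | 68.4% | 5.5 | 9.7% |
| 3.74 | 34.5% | 3.76 | about 34% |

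The 87.2% is therefore the power only when there is no offset.

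**Step 3: what adjustment does to precision.** Assume a true adjusted difference of zero and 5 covariate degrees of freedom. Let r be the correlation of the covariates with week-12 MCS-12, and v the variance inflation from imbalance between the groups. The article gives neither.

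| | v = 1 | v = 1.1 | v = 1.25 |
|---|---|---|---|
| r = 0 | 87.1% | 82.0% | 73.4% |
| r = 0.3 | 91.2% | 87.1% | 79.9% |
| r = 0.5 | 96.5% | 94.3% | 90.0% |

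With a moderately prognostic baseline score, adjustment keeps or raises power. It loses power when the covariates are imbalanced but weakly prognostic.

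**The case against.** The strongest reply has four parts.

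- **The article is condensed.** A covariate list and model form normally sit in the full protocol or analysis plan, and sizing on an unadjusted difference does not forbid an adjusted interval. This is right as far as it goes: a missing covariate list alone would be no finding. But the article goes further and states a univariate analysis, described as being between randomised groups, while a main comparison is not randomised. An analysis plan written to match it would carry the problem forward.

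- **More than a crude test is planned.** A reader might infer that comparison 2 gets only an unadjusted test, or that the article passes the metropolitan group off as randomised. Neither is supported. The article never uses the word unadjusted for this test, it plans a longitudinal analysis that could hold covariates, and the Design section is open about how the group is formed. What stands is that the longitudinal analysis names no confounder and is not tied to this comparison.

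- **The created-equivalence risk can be overstated.** A reader might note that a 2-point favourable offset raises the chance of declaring equivalence from 34.5% to about 73% when the intervention group is truly 3.74 points worse, and call that false equivalence. It is not: 3.74 lies inside the plan's ±7.5 bound, so equivalence is the correct conclusion there by the plan's own definition. The false-positive rate has to be judged at the bound, as in the table.

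- **An unadjusted contrast may be wanted.** The sample size section speaks of bringing parents up to the metropolitan level, which can be read as a parity benchmark that adjustment would alter. Hypothesis 2, on effectiveness of support, points to the like-for-like reading. Both readings are open, which is a reason to report both estimates.

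**Conclusion.** The point stands. Intervention versus metropolitan is a main comparison, it is not randomised, and nothing in the stated methods keeps baseline differences out of its equivalence result. Under the assumed offsets of 1 to 3.74 points, the chance of declaring equivalence when support is truly equal falls from 87.2% to between 82.2% and 34.5%. False equivalence at the bound rises from 1% to between 3.5% and about 34%.

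These figures rest on SD 10, 54 per group, 1% per one-sided test and offsets that the article neither gives nor rules out. They show sensitivity; they do not estimate a bias known to be present. At 1 point the loss of power is modest. The randomised comparison of the two regional groups is unaffected. The change should be made, but the point does not put the trial as a whole in doubt.

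**What to change.** For comparison 2:

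1. Base the equivalence interval on the MCS-12 difference adjusted for baseline MCS-12 and a short prespecified list of baseline factors. Use the demographics already collected, and diagnosis if it can be taken from the chart audit; the Measurement section does not name diagnosis as a collected item.
2. Report the unadjusted difference alongside as the parity benchmark, and say which of the two answers hypothesis 2.
3. Describe the comparison as a non-randomised contrast with possible residual confounding. ARIA+ separates the two groups completely, so effects of residence itself cannot be adjusted away.
4. In the Statistical analysis section, limit the randomised-groups wording to comparison 1.

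The cost is a change of wording and a little more analysis, with no new interviews. The downside is a possible loss of precision if the covariates are imbalanced but weakly prognostic: with r = 0, power is 82.0% at 10% variance inflation and 73.4% at 25%.

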#### Economic analysis

It is hypothesised that using videotelephony will be a cost-effective method of service delivery. Economic evaluation will be investigated in four areas.

1. The cost of providing improved support

- The potential for videotelephony to improve the health related quality of life of parents comes at a cost. The total cost of providing the videotelephone service will be calculated including project establishment costs, equipment costs, maintenance costs, communication costs and staff costs.

2. Health care use savings

a. *Use of local health services*

- The improved support provided by videotelephony has the potential to reduce the need for parents and patients to access local health care services. These include (but are not limited to) community nursing visits, general practitioner consultations, psychosocial health care consultations, respite care, emergency room visits and local hospital admissions. The improved support is not intended to minimise the much needed and valued local community support. Instead, the improved support provided by the videotelephone service reduces the need to burden these services for reasons that can be avoided with improved specialist support (i.e. improved symptom management, improved continuity of care, improved psychosocial support, improved care planning and improved emergency management).

b. *Use of the entire health system*

- To investigate the effect on costs to the health system, health care use data will be gathered. Information on health care encounters (including in-patient, outpatient, emergency department, general practitioner, home care and respite care instances) will be collected from families in the intervention and control groups with bi-weekly telephone interviews. Hand searching of patient medical records will be completed to determine and verify all health care encounters. Encounters will be valued according to the Australian Medicare Benefits Schedule of resource items and their associated costs.

3. Reduced financial burden for families

- Families may also benefit financially from the improved support provided by the videotelephone service. Improved support has the potential to reduce the need for travel and associated costs. Information on family out-of-pocket expenses (such as travel costs including fuel, parking, fares; and other costs including meals, child care and accommodation) will also be obtained to assess the direct non-medical financial impact on families and how effectively the videotelephone service reduces this impact.

4. Cost-effectiveness analysis

- The health system perspective will be used for the primary analysis, and will be augmented in subsequent analysis with direct non-medical costs. The costs of providing the videotelephone service plus the total cost of health service use for the intervention group will be compared to the total cost of health service use identified in the regional and remote usual support control group. This is the incremental cost.

- Using the *Research Instruments *listed above, differences between the intervention group and the regional and remote usual support control group will be calculated. From this, the incremental cost per additional unit of benefit gained will be calculated, i.e. the incremental cost-effectiveness ratio (ICER); e.g. it costs an additional $x to improve parental quality of life by 1 point.

- A cost-utility analysis will also be undertaken. This allows comparisons between programs to be made and hence value for money judgements, as outcomes are standardised into quality-adjusted life years (QALYs). QALYs will be calculated using the HUI2 and the SF-6D algorithm to convert the SF-12 scores into utility scores (where 0 = dead, and 1.0 = best imaginable health state) and multiplied by the duration of life in that health state [37]. Differences in QALYs (for both parents and patients) between groups will be used to estimate the incremental cost-utility ratios.

- Sensitivity analyses will be conducted around the variables with the greatest uncertainty as well as the duration of final utility score at the end of the 12-week follow-up.

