## Abstract

**Background:**

Providing ongoing family centred support is an integral part of childhood cancer care. For families living in regional and remote areas, opportunities to receive specialist support are limited by the availability of health care professionals and accessibility, which is often reduced due to distance, time, cost and transport. The primary aim of this work is to investigate the cost-effectiveness of videotelephony to support regional and remote families returning home for the first time with a child newly diagnosed with cancer

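### All health care encounters, including admissions, emergency visits, home care and respite care, are priced from one benefits schedule, which can bias the incremental cost by an unknown amount if their use differs between arms

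*Protocol article*

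**What the plan says.** The abstract of the protocol article makes cost-effectiveness the leading purpose: "The primary aim of this work is to investigate the cost-effectiveness of videotelephony to support regional and remote families returning home". Hypothesis 3 repeats it.

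Under Economic analysis, item 2b (use of the entire health system), the encounters to be collected are listed as "in-patient, outpatient, emergency department, general practitioner, home care and respite care instances". The same paragraph then prices them: "Encounters will be valued according to the Australian Medicare Benefits Schedule of resource items and their associated costs". No encounter type is excepted, and no other price source is named anywhere in the economic section.

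Item 2a lists the local services whose use the intervention might reduce: "community nursing visits, general practitioner consultations, psychosocial health care consultations, respite care, emergency room visits and local hospital admissions".

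Item 1 costs the videotelephone service differently, component by component: establishment, equipment, maintenance, communication and staff.

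Item 4 brings the two together. On perspective: "The health system perspective will be used for the primary analysis, and will be augmented in subsequent analysis with direct non-medical costs". On the calculation: "The costs of providing the videotelephone service plus the total cost of health service use for the intervention group will be compared" with the total cost of health service use in the regional and remote usual support control group. The difference is the incremental cost.

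**The concern.** A health system perspective calls for the resource cost of each encounter: staff, beds, supplies and overheads. A schedule of benefits, judged by its name, sets out amounts payable for itemised services. That is a natural price for a general practitioner or specialist consultation. It is not obviously a price for a hospital stay, an emergency attendance, a home care visit or a respite day, yet item 2b applies it to all of them.

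The two sides of the incremental cost would then be measured on different bases. The new service is charged at its resource cost, while the care that it may replace, or generate, is credited or charged at a scheduled benefit. The same incremental cost is the numerator of the cost-effectiveness ratio and of the cost-utility ratios for parents and patients, so an error in it carries into every economic ratio. The SF-12 comparison, which is the primary outcome, is not affected.

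**Working it through.** The article gives no unit costs, no expected encounter counts and no expected saving, so there is no costing figure to reproduce. Its sample size and equivalence power do not enter this question. The check is therefore a comparison of the stated rules, followed by the algebra that they imply.

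**Rules side by side (Economic analysis)**

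- Item 1: the service is costed by resource component.
- Item 2b: six named encounter types, one price source, no exception.
- Item 4: health system perspective; service cost plus priced use in the intervention arm, minus priced use in the regional and remote control arm.

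**Direction of the error**

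Define, per family at full resource cost:

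- S = cost of the videotelephone service;
- T1 = reduction in use (control minus intervention) of consultations that the schedule prices adequately;
- T2 = the same reduction for hospital, home and respite care;
- c = fraction of the resource cost of the T2 items that the schedule recovers.

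True incremental cost = S − T1 − T2.

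Incremental cost under the plan = S − T1 − c·T2.

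Error = plan minus true = (1 − c)·T2.

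For c below 1:

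- T2 > 0 (use falls): the incremental cost is overstated, against the service.
- T2 < 0 (use rises): the incremental cost is understated, in favour of the service.
- T2 = 0 (no difference between arms): no error, whatever c is.

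With a positive health gain E, the ICER is off by (1 − c)·T2 / E, in the same direction.

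**Illustration only**

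Suppose both kinds of use fall. Let T = T1 + T2, and let w = T2/T be the share of the true saving that lies in the poorly priced types. The share of the saving that the plan captures is

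k = (1 − w) + w·c.

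Neither w nor c can be taken from the documents. With assumed ranges w = 0.3 to 0.9 and c = 0 to 0.5:

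| w | c = 0 | c = 0.5 |
|---|---|---|
| 0.3 | 0.70 | 0.85 |
| 0.6 | 0.40 | 0.70 |
| 0.9 | 0.10 | 0.55 |

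So k runs from 0.10 to 0.85. The plan would report a cost increase where there is a true saving whenever kT < S < T. At k = 0.85 that needs S between 85% and 100% of T; at k = 0.10, between 10% and 100%. The table shows how strongly the answer depends on inputs that the documents do not give. It is not an estimate of the bias.

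**The case against.** **The documents do not describe the schedule's contents.** This stands. That the schedule does not give full resource costs for hospital, home and respite care is an inference from what a benefits schedule is, not something the article states. The closing words of the valuation sentence, which speak of costs attached to the schedule's items, are somewhat broader than a fee list. Read grammatically, though, they refer to the schedule's own items and supply no second source.

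**A condensed article leaves unit costs to a fuller plan.** This is true of a unit-cost table or a price year, and their absence alone would be no finding. Here the article states a valuation rule and applies it to all encounters. The point is the rule.

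**The planned sensitivity analyses might cover it.** Item 4 plans them around the most uncertain variables, and unit costs could be among these. They are not named, no alternative price is given, and the base case would still rest on the schedule.

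**A reader might infer that the plan leaves out most of the intended saving, or credits an avoided admission with next to nothing.** The documents do not support that. The services in item 2a also include general practitioner and psychosocial consultations, some of which the schedule may price adequately, and the captured share above passes one half in several cells of the table. Nor would the share of total cost per family captured by the schedule measure the bias in the ICER, which depends on the difference between arms.

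**Community nursing is not in the list to be priced.** It is named only in item 2a. The list in 2b is open and includes home care, so community nursing may be covered, but the article does not say so.

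**Conclusion.** The concern holds in a limited form. The article fixes one benefits schedule as the price source for every encounter type, takes a health system perspective, and sets the result against a service costed by resource. If use of hospital, home or respite care differs between the regional and remote arms, the incremental cost and the ICER can be biased: against the service if use falls, in its favour if it rises. If use does not differ, these prices introduce no bias.

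The conclusion assumes that the schedule recovers less than the full resource cost of those services (c below 1) and, for the ICER, that the health gain is positive. The size is unknown, because the documents give neither unit costs nor encounter mix. The point deserves correction because the abstract makes cost-effectiveness the primary aim and the remedy is inexpensive.

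**What to change.** Replace the single valuation sentence in item 2b with a price source for each encounter type:

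- general practitioner, specialist and other scheduled consultations: the Medicare Benefits Schedule, as now;
- admissions, emergency department and hospital outpatient attendances: hospital costing or casemix cost data;
- home care, community nursing and respite care: provider unit costs.

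Use one price year, and state whether community nursing visits are among the encounters collected. Schedule-only valuation can be kept as a named sensitivity analysis. Fix the sources before use by arm is known, so that prices cannot be chosen in the light of the results.

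The cost is new wording and a unit-cost table. The encounter counts already planned, checked against medical records, are enough; sample size and interview schedule do not change. The small downside is that unit costs would come from several sources and need to be put on a common basis.

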### Participants

Patients of the Royal Children's Hospital Haematology, Oncology and Stem Cell Transplant Unit will be identified by their paediatric oncologist before first discharge home. To be included in the study patients will be: newly diagnosed male or female paediatric oncology patients aged 2–18 years. Patients will be excluded if a home telephone connection of satisfactory quality cannot be installed.

The paediatric oncology clinical nurse consultants responsible for each patient will approach the family individually. Families will be asked to participate in a project investigating the use of videotelephones for supporting children with cancer and their families. A brief overview of the project will be provided before each family is asked if they consent to talk with a research assistant about the project.

The research assistant responsible for the project will provide written information on the trial informing all potential participants about the study, the frequency, content and expected duration of telephone interviews and what their participation would entail before obtaining consent.

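### The incremental cost is set as a plain difference in all-encounter totals across mixed cancer diagnoses; prespecified adjustment for diagnostic group would sharpen it at almost no cost

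*Protocol article*

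**What the plan says.** All references are to the protocol article.

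- **Aim.** Abstract, Background: "The primary aim of this work is to investigate the cost-effectiveness of videotelephony". Hypothesis 3 is that videotelephony will be cost-effective.
- **Perspective.** Economic analysis, item 4: "The health system perspective will be used for the primary analysis".
- **Estimator.** Same item: the cost of the service plus total health-service cost in the intervention group "will be compared to the total cost of health service use identified in the regional and remote usual support control group". The article names this difference the incremental cost, and it feeds the cost-effectiveness and cost-utility ratios.
- **What is counted.** Economic analysis, item 2b, covers encounters "including in-patient, outpatient, emergency department, general practitioner, home care and respite care instances", and adds: "Hand searching of patient medical records will be completed to determine and verify all health care encounters".
- **Population.** Participants: "newly diagnosed male or female paediatric oncology patients" aged 2–18 years, with no restriction on diagnosis.
- **Allocation.** Randomization: odd or even entries in a table of random numbers. No stratification is described.
- **Analysis.** Statistical analysis: univariate comparison of randomised groups on primary and secondary outcomes, then longitudinal methods for within-family correlation and change over time. The Abstract lists cost and health care utilisation among the secondary outcomes.

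**The concern.** Cancers that differ in treatment can be expected to differ in 12-week cost. That between-diagnosis spread enters the total in both arms. Neither the allocation method nor the stated analysis removes it, so a chance excess of children with costly treatment in one arm passes straight into the incremental cost. At stake is the precision of the cost side of the primary aim. Part of the uncertainty comes from a characteristic known before allocation, so it could be removed in the analysis. Prespecification also prevents an adjustment being chosen after the costs have been seen.

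**Working it through.** **The plan's own figure.** The 54 per arm is derived from the SF-12 mental score: difference 7.5, SD 10, two-sided 1%, 90% power. The normal formula 2 × (2.576 + 1.282)² × (10/7.5)² gives 53 per arm; at 54 per arm, power is 90.7% (normal) or 89.6% (t). The figure therefore reproduces, but it says nothing about costs. The sample size section announces calculations for the economic analyses, yet no cost calculation follows and no cost SD is given.

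**Assumed inputs (not in the article).**
- Coefficient of variation (CV) of 12-week cost per family: 0.8 to 1.2.
- Share of children on costlier treatment: p = 0.40.
- Cost ratio of that group to the rest: k = 2 to 4.
- Share of cost variance explained by diagnosis: R² = 0.2 to 0.5.

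**Step 1: precision of the unadjusted difference.** SE as a fraction of mean cost = CV × √(2/54) = CV × 0.1925.
- CV 0.8: 15.4%. CV 1.0: 19.2%. CV 1.2: 23.1%.
- 95% half-width (1.96 × SE): 30%, 38% and 45% of mean cost.

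**Step 2: effect of chance imbalance.** SD of the difference in shares = √(2 × 0.4 × 0.6/54) = 0.094, or 9.4 percentage points. The shift in the cost difference for a one-SD imbalance, relative to mean cost, is 0.094 × (k − 1)/(0.4k + 0.6).
- k = 2: 6.7%. k = 3: 10.5%. k = 4: 12.9%.

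**Step 3: how much of the noise this is.** The share of cost variance is (step 2 ÷ step 1)², which equals 0.24 × [(k − 1)/(0.4k + 0.6)]²/CV².

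| | CV 0.8 | CV 1.0 | CV 1.2 |
|---|---|---|---|
| k = 2 | 19% | 12% | 8.5% |
| k = 3 | 46% | 30% | 21% |
| k = 4 | 70% | 45% | 31% |

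Eight of the nine combinations lie between 8.5% and 46%. Only one exceeds half.

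**Step 4: gain from adjustment.** SE ratio = √(1 − R²).
- R² = 0.2: 0.894, a cut of 11%. R² = 0.3: 0.837, a cut of 16%. R² = 0.5: 0.707, a cut of 29%.
- The same precision without adjustment needs 1/(1 − R²) times as many families: 25% more at R² = 0.2 and 100% more at R² = 0.5.
- In the least favourable cell of step 3 (8.5%), the cut is only 1 − √0.915 = 4%.
- At R² = 0.5 the 95% half-width falls from 30%–45% to 21%–32% of mean cost. That is better, but still wide.

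**The case against.** **The article condenses a fuller plan.** It never calls the cost comparison unadjusted, and covariates for a cost model are commonly left to an analysis plan. This stands in part. Against it, the article does define the incremental cost as one total against another, and its only stated between-group outcome analysis is univariate. Adjustment would therefore change the stated method, not merely fill in a detail.

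**The measure is legitimate and the estimate unbiased.** Both points stand. An all-encounter total suits a health-system perspective, and randomisation protects the comparison.

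**Stronger readings that the article does not support.**
- *The service can act only on avoidable encounters.* Item 2a says that better support "reduces the need to burden these services for reasons that can be avoided with improved specialist support", but that concerns local services and does not say these are the only effect. Item 2b separately examines the whole health system.
- *Planned treatment, fixed before allocation, is beyond the reach of the service.* The article does not mention scheduled treatment. In-patient totals would also include unplanned admissions that the service might change.
- *Diagnosis is the main source of noise, or swamps the answer.* Under the assumed inputs it passes half of the variance in one cell of nine.
- *A change of sign in the incremental cost would overturn hypothesis 3.* Item 4 itself illustrates the result as a positive cost per point of parental quality of life gained. A positive incremental cost is therefore compatible with cost-effectiveness.

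**The planned sensitivity analyses might cover it.** They address the most uncertain variables and the duration of the final utility score. Diagnosis mix is not named.

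**Conclusion.** The point holds as an avoidable loss of precision in the cost side of the primary aim, not as a bias or an error. Under the assumed cost inputs, a one-SD chance imbalance in diagnosis moves the incremental cost by 7% to 13% of mean cost. Adjustment explaining 20% to 50% of cost variance would cut its SE by 11% to 29%. The imbalance figure needs only 54 per arm and the assumed 40% share; everything in cost terms depends on the assumed CV, cost ratio and R², because the article supplies none of these. If diagnosis explains little of the cost, the gain is small. Adjustment would not by itself make the cost comparison precise.

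**What to change.** Keep the health-system, all-encounter total as the cost measure. In the analysis plan:

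1. Estimate the incremental cost for the base-case cost-effectiveness and cost-utility ratios by regression of per-family 12-week cost on arm, adjusted for diagnostic group. An identity link keeps the arm coefficient a difference in mean cost.
2. Prespecify a small number of diagnostic groups, taken from information recorded before allocation and fixed before any cost data are seen.
3. Give bootstrap intervals, resampling families within arm so that cost and effect stay paired.
4. Report the unadjusted difference alongside.

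A breakdown into scheduled and unscheduled encounters is optional and descriptive only. It would be made after randomisation and needs a judgement on each encounter.

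The cost is analysis-plan wording and one diagnosis field, which should be available from the medical records already to be searched. No patients, visits or interviews are added.
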